In a recently published systematic review, Stein et al [6] evaluated thirty five short term randomized controlled medication trials for PTSD (4597 participants). In thirteen trials, response to medication occurred in 59.1% of patients (644 participants), while response to placebo was seen in 38.5% of patients (628 participants). Significant reductions in symptom severity were observed for patients who received medications in seventeen trials. The mean total CAPS score for the medication group was 5.76 points lower than that for the placebo group (95% CI – 8.16 to -3.36 and 2507 participants). Evidence of treatment efficacy was most convincing for the SSRIs. Furthermore, medication was superior to placebo in reducing the severity of the three symptom clusters of PTSD, as well as alleviating the symptoms of depression, and in improving the quality of life measures. The current evidence base of randomized clinical trials is unable to demonstrate superior efficacy or acceptability for any particular medication class.

Nevertheless, the bulk of evidence for the efficacy of medication has been with the SSRIs and supports expert consensus guidelines that these medications constitute the first-line medication choice in PTSD.

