Clinical studies with topiramate suggest that it is effective as monotherapy or adjunctive therapy in PTSD. Two open-label studies demonstrated topiramate to be effective and to have a rapid onset of action. Berlant and van Kammen [27] have reported that topiramate decreased nightmares in 79% and flashbacks in 86% of civilian patients with chronic PTSD with improvement of nightmares in 50% and of intrusions in 54% of patients with these symptoms. A partial response was reported for 95% of patients at a dosage of 75 mg/day or less and in 91% of full responders at a dosage of 100 mg/day or less. The nonhallucinatory subgroup achieved a higher response rate (89%). In a prospective open-label study, Berlant [28] treated thirty three civilians with chronic PTSD, with topiramate as monotherapy or augmentation therapy. The PTSD Checklist-Civilian Version (PCL-C) total symptoms declined by 49% at 4th week, with similar subscale reductions for reexperiencing, avoidance/numbing, and hyperarousal symptoms. Topiramate suppressed nightmares in 79% and decreased symptoms of intrusions in 94% in those patients with these symptoms. There is only one double-blind, placebo- controlled study of topiramate as a monotherapy in PTSD. Tucker [29] conducted a 12-week, double-blind, placebo-controlled evaluation of topiramate as a monotherapy in thirty eight civilian PTSD patients. Patients in the topiramate group exhibited significant reductions in reexperiencing symptoms (CAPS cluster B: topiramate = 74.9%; placebo = 50.2%; p = .038) and reductions approaching statistical significance, based on a nominal p value, were noted in mean total Clinical Global Impressions-Improvement Scale scores (topiramate = 1.9 ± 1.2; placebo = 2.6 ± 1.1; p = .055). Although there was a reduction in total Clinician-Administered PTSD Scale (CAPS) score from baseline (topiramate = -52.7; placebo = -42.0), the difference was not statistically significant (p = .232). But not all studies found positive results, Lindley [30] in a double-blind, placebo-controlled study using topiramate as an augmentation therapy in forty male veterans with PTSD did not find significant treatment effects versus placebo. However, there was a high dropout rate from the study with 11 (55%) topiramate and 5 (25%) placebo subjects not completing the seven week treatment, with 40% of topiramate and 10% of placebo dropping because of adverse effects. Patients in the topiramate group that completed the study, had a significant improvement in the reexperiencing subscale of the CAPS suggesting efficacy for the patients that continued the medication.

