### Aims of the Study

1) To compare the efficacy of topiramate with placebo in the treatment of PTSD. Clinical response will be considered when there are a 20% reduction on CAPS scale scores from baseline and remission when CAPS score is less than 19.

2) To study the tolerability of topiramate in the treatment of PTSD, through the dropout rate in each group.

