### Sample Size

The number of subjects calculated for the trial is 72, being 36 on each cell. The sample size was calculated considering a 5% probability of type I error (significance level), and 20% for type II error (power test of 80%), on a bi-caudal test. To the calculation we use an average of 60% for response from PTSD for active drugs, based on published literature, and 30% of placebo response.

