### Statistical Analysis

All data will be analyzed by SPSS (version 13.0). The frequencies of nominal variables from all patients will be calculated. The data analysis will be conducted using a ANOVA comparing each scale during the 2 continuous measures from baseline and 12 weeks with a Between Subject factor was included as independent variable (treatment group). The confidence level that will be used for all comparisons will be 5% (p < .05). All observed Power as a type II error function will be presented with minimum values of significance for each comparison. CAPS scores from baseline and endpoint will be stratified according severity, as nominal data they will be compared using the chi-square test and the Fisher test when there were cells that counted less than five or at least one cell counted zero subjects. For missing data we will use the last observation carried forward strategy for an intention-to-treat analysis.

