Efficacy analyses will be performed in the intent-to-treat population of patients who received at least one dose of topiramate. The primary efficacy endpoint will be the change in PTSD Scale- CAPS total score from baseline to the final visit at 12 weeks, which will be compared between treatment groups. Missing efficacy data at 12 weeks will be imputed with the last observation carried forward. The secondary outcomes between groups will be comparing the Clinical Global Impressions (CGI), the Beck Depression Inventory (BDI), the Global Assessment of Function (GAF), and the PANAS scales. Other secondary analyses will include an evaluation after 24-weeks (12-week after last patient visit with drug) data with endpoint analyses between the treatment groups covarying for baseline scores. On all secondary outcomes, the Bonferroni correction will be applied for testing multiple variables. Response will be defined as a 20% improvement in the baseline CAPS total or positive symptom scores at 12 weeks and will be compared between treatment groups using a chi-square test. Proportions of patients completing the 12-week double-blind study will be compared between treatment groups using a chi-square test. Adverse events reported by 10% of patients in each treatment group will be compared using a chi-square test. Laboratory values, vital signs and physical examinations are going to be compared from baseline and in reference to normal ranges, and reported as normal or abnormal. Changes in body weight (lb), body mass index (BMI; kg/m2) at last visit in the 12-week dataset will be compared as mean changes between treatment groups using t-tests.

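### The stated 80% power is for a responder comparison, not for the primary endpoint of CAPS change, and 36 per arm gives only about 73% even for that comparison

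*Protocol article*

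**What the plan says.** The Sample Size section sets 72 patients, 36 per arm, for a two-sided 5% test with 80% power. Its only effect assumption is a pair of response rates: "we use an average of 60% for response from PTSD for active drugs, based on published literature, and 30% of placebo response". As worded, the reference to literature attaches to the 60%; no source is given for the 30%.

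The Statistical Analysis section fixes a different, continuous outcome as primary: "The primary efficacy endpoint will be the change in PTSD Scale- CAPS total score from baseline to the final visit at 12 weeks". The Abstract agrees. The comparison is an ANOVA on baseline and week 12 with treatment group as the between-subject factor. Response is a separate chi-square comparison, defined under Aims of the Study: "Clinical response will be considered when there are a 20% reduction on CAPS scale scores from baseline".

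The Background supplies figures that bear on both calculations:
- A systematic review of medication trials reports 59.1% response on drug, while "response to placebo was seen in 38.5% of patients (628 participants"), and a CAPS difference of 5.76 points.
- The only placebo-controlled monotherapy trial of topiramate, with 38 patients, reports mean CAPS changes of ("topiramate = -52.7; placebo = -42.0), the difference was not statistically significant (p = .232").

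On reporting, the Statistical Analysis section says: "All observed Power as a type II error function will be presented with minimum values of significance for each comparison".

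**The concern.** The only power figure in the document belongs to a comparison that does not decide the trial. For the one that does, the reader cannot tell what difference 72 patients could detect. The placebo rate of 30% also looks optimistic beside the Background. A 20% fall in CAPS is a low bar, and the mean placebo patient in the cited monotherapy trial fell by 42.0 points.

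At stake is how a non-significant result is read. If the trial is described as having 80% power, such a result is likely to be taken as evidence that topiramate does not work. Observed power computed after the fact would not correct that reading, because it only restates the p value.

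**Working it through.** **1. The plan's own figure.** Inputs from Sample Size: p1 = 0.60, p2 = 0.30, two-sided 5% (z = 1.960), 80% power (z = 0.842). The mean proportion is 0.45.

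n per arm = [1.960 × √(2 × 0.45 × 0.55) + 0.842 × √(0.60 × 0.40 + 0.30 × 0.70)]² / 0.30² = (1.379 + 0.565)² / 0.09 ≈ 42.0

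Power at 36 per arm = Φ[(0.30 × √36 − 1.379) / √0.45] = Φ[(1.800 − 1.379) / 0.671] = Φ(0.628) = 73.5%

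Other two-sided methods:

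| Method | n per arm for 80% | Power at 36 per arm |
|---|---|---|
| Pooled normal | 42 | 73.5% |
| Unpooled normal | 40 | 76.5% |
| Arcsine | 42 | 73.9% |
| Continuity-corrected | 49 | – |
| Exact enumeration, chi-square | – | 72.7% |
| Exact enumeration, Fisher | – | 63.6% |

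One-sided versions give 31 to 33 (40 with continuity correction), but the plan states a two-sided test. No method tried gives 36.

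**2. The placebo rate.** With the Background's 59.1% versus 38.5%, the mean proportion is 0.488:

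Power at 36 per arm = Φ[(0.206 × 6 − 1.960 × √(2 × 0.488 × 0.512)) / √(0.591 × 0.409 + 0.385 × 0.615)] = Φ[(1.236 − 1.386) / 0.692] = Φ(−0.216) = 41%

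That comparison needs 92 per arm for 80% power. Keeping 60% on drug against 38.5% gives 44%.

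Under the 20% cut, the largest possible threshold is 0.20 × 136 = 27.2 points, 136 being the scale maximum given under Measures. The cited mean placebo fall is 42.0. Assuming normal changes, the placebo share above that threshold is Φ[(42.0 − 27.2) / SD]: 77% at SD 20, 71% at SD 27, 66% at SD 35. Any baseline below 136 lowers the threshold and raises the share.

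**3. An SD for CAPS change.** The documents give none, so this is an assumption. The monotherapy trial reports a difference of 52.7 − 42.0 = 10.7 with p = .232 in 38 patients. Take a plain t-test with 19 per arm (36 df). Then t = 1.216, SE = 10.7 / 1.216 = 8.80, and SD = 8.80 / √(2/19) = 27.1. A 15/23 split gives 26.5.

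**4. Power for CAPS change at 36 per arm.** With two time points, the group-by-time test in the ANOVA is equivalent to a t-test on change scores. Using the noncentral t with 70 df and noncentrality (difference / SD) × √(36/2), 80% power needs 0.67 SD:

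| Assumed SD | Detectable at 80% | Power for 10.7 points | Power for 5.76 points |
|---|---|---|---|
| 20 | 13.4 points | 61% | 23% |
| 27 | 18.1 points | 38% | 15% |
| 35 | 23.4 points | 25% | 11% |

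**5. Where the shortfall comes from.** If 60% versus 30% were true on a normal latent scale, the standardised difference would be 0.253 + 0.524 = 0.78, and 36 per arm would give about 90% power on the mean.

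**6. Observed power.** On the normal scale it is a function of p alone. At p = .05 it is Φ(1.96 − 1.96) = 50%; at p = .232 it is about 22%.

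**The case against.** Several counter-arguments have force.

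- **The change of endpoint does not itself cost power.** Step 5 shows that under the plan's assumed effect the continuous outcome would do better than response. This stands. A reader might infer that the mismatch causes the low power; the low figures come from the cited CAPS differences.
- **The power range is conditional.** A reader might take 15% to 40% as the trial's actual power for its primary endpoint. The documents do not support that. The SD comes from one p value, with equal arms, all 38 patients analysed and a plain t-test assumed. The 5.76 points pool many drugs. The 10.7 points carry a 95% interval of about −7 to 28.5 on the same assumptions (10.7 ± 2.03 × 8.80), which includes the 18 points that are detectable. So the trial is not shown to be incapable of detecting a plausible effect.
- **The 30% is not strictly contradicted.** It is tempting to say the Background refutes it. But the Background does not define the review's response, so 38.5% need not mean a 20% CAPS fall. The Wash-out phase also removes patients who improve on placebo, which could lower the later placebo rate somewhat. The two rates are in tension, no more.
- **Sizing on response is not alien to this trial.** The first aim defines efficacy partly through response. True, but the primary endpoint is named without ambiguity as CAPS change.
- **Observed power is a small reporting matter, and intervals are often left to an analysis plan.** It is minor. Still, the article itself commits to observed power, so this is a stated choice and not an omission.

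None of this touches the arithmetic in step 1, which uses only the plan's own inputs.

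**Conclusion.** The point holds in two parts that need no outside assumption. The stated 80% does not refer to the primary endpoint, and it is not reached for the comparison to which it does refer: about 73% at 36 per arm, with about 42 per arm needed.

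The rest is conditional. The 30% placebo rate is unsourced, below the cited 38.5%, and hard to square with a 20% cut given a mean placebo fall of 42.0 points. For CAPS change at an assumed SD of 27, the detectable difference is about 18 points, larger than either between-group difference the Background cites. Across SD 20 to 35, power for both cited differences stays below 80% (11% to 61%). These figures depend on the assumed SD and on taking the cited effects as the ones of interest.

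**What to change.** No patients need be added.

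1. In Sample Size, state the power or detectable difference for CAPS change at 36 per arm. Label the SD as an assumption and show a range: for example, about 18 points at SD 27, and 13 to 23 points over SD 20 to 35, with power at 10.7 and 5.76 points.
2. Label the response calculation secondary and correct its power to about 73% at 60% versus 30%. Add a sensitivity range for higher placebo response at the plan's own 20% cut. Simply substituting 38.5% would not do, since step 2 suggests that the rate at this cut could be well above it.
3. In Statistical Analysis, replace observed power with the between-group difference and its 95% confidence interval.

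The cost is one rewritten paragraph and one sentence. The downside is that the stated power becomes less favourable.

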### Statistical Analysis

All data will be analyzed by SPSS (version 13.0). The frequencies of nominal variables from all patients will be calculated. The data analysis will be conducted using a ANOVA comparing each scale during the 2 continuous measures from baseline and 12 weeks with a Between Subject factor was included as independent variable (treatment group). The confidence level that will be used for all comparisons will be 5% (p < .05). All observed Power as a type II error function will be presented with minimum values of significance for each comparison. CAPS scores from baseline and endpoint will be stratified according severity, as nominal data they will be compared using the chi-square test and the Fisher test when there were cells that counted less than five or at least one cell counted zero subjects. For missing data we will use the last observation carried forward strategy for an intention-to-treat analysis.

Efficacy analyses will be performed in the intent-to-treat population of patients who received at least one dose of topiramate. The primary efficacy endpoint will be the change in PTSD Scale- CAPS total score from baseline to the final visit at 12 weeks, which will be compared between treatment groups. Missing efficacy data at 12 weeks will be imputed with the last observation carried forward. The secondary outcomes between groups will be comparing the Clinical Global Impressions (CGI), the Beck Depression Inventory (BDI), the Global Assessment of Function (GAF), and the PANAS scales. Other secondary analyses will include an evaluation after 24-weeks (12-week after last patient visit with drug) data with endpoint analyses between the treatment groups covarying for baseline scores. On all secondary outcomes, the Bonferroni correction will be applied for testing multiple variables. Response will be defined as a 20% improvement in the baseline CAPS total or positive symptom scores at 12 weeks and will be compared between treatment groups using a chi-square test. Proportions of patients completing the 12-week double-blind study will be compared between treatment groups using a chi-square test. Adverse events reported by 10% of patients in each treatment group will be compared using a chi-square test. Laboratory values, vital signs and physical examinations are going to be compared from baseline and in reference to normal ranges, and reported as normal or abnormal. Changes in body weight (lb), body mass index (BMI; kg/m2) at last visit in the 12-week dataset will be compared as mean changes between treatment groups using t-tests.

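### The primary 12-week CAPS comparison carries no baseline covariate, although baseline CAPS is collected and the 24-week analysis adjusts for it; ANCOVA would be at least as precise for one degree of freedom

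*Protocol article*

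**What the plan says.** The Statistical Analysis section of the protocol article sets one model for the 12-week data: "The data analysis will be conducted using a ANOVA comparing each scale during the 2 continuous measures from baseline and 12 weeks". Treatment group is the between-subject factor, and no covariate is named. The same section makes change in CAPS total from baseline to week 12 the primary efficacy endpoint, compared between the groups, again without a covariate.

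Baseline adjustment appears once, for a secondary evaluation at 24 weeks, described as "endpoint analyses between the treatment groups covarying for baseline scores".

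The Screening Phase section has trained raters administer the CAPS before treatment, so the covariate will be in hand.

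The Statistical Analysis section also promises that "All observed Power as a type II error function will be presented with minimum values of significance for each comparison".

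**The concern.** With two time points, the group-by-time term of a repeated-measures ANOVA is the same test as a t-test on change scores. A change score fixes the slope of week-12 score on baseline at 1. When the true slope is below 1, it over-corrects for chance baseline differences and adds noise. ANCOVA estimates the slope from the data and so avoids this loss.

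The plan applies baseline adjustment to a secondary analysis and leaves it out of the primary one. With 36 patients per arm, any avoidable loss of precision in the primary comparison matters.

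Observed power is a smaller issue of reporting. It is a re-expression of the p-value (about 50% when p = .05), so it cannot help a reader to interpret a non-significant result.

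**Working it through.** **The plan's own figure.** The Sample Size section gives no power figure for the CAPS change. It sizes the trial on a binary response: "we use an average of 60% for response from PTSD for active drugs", against "30% of placebo response", "considering a 5% probability of type I error (significance level") and "20% for type II error (power test of 80"%), "on a bi-caudal test". The pooled two-proportion formula is n per arm = [1.960·√(2·0.45·0.55) + 0.842·√(0.6·0.4 + 0.3·0.7)]² / 0.30². It gives 41.97, so 42 per arm (84 in total). The stated 36 per arm has about 73% power. That mismatch is a separate matter, and nothing below depends on it except the 36 per arm.

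**Inputs.**
- 36 per arm, two-sided 5% (Sample Size).
- Effect: the Background reports CAPS changes of −52.7 on topiramate and −42.0 on placebo in the cited 38-patient monotherapy trial. The difference is 10.7, p = .232.
- SD of change: not given. Assuming 19 per arm and a t-test on 36 df, p = .232 corresponds to t = 1.216. Then SE = 10.7/1.216 = 8.80 and SD = 8.80/√(2/19) = 27.1, taken as 27.
- rho, the baseline to week-12 correlation: not given. Assumed to be 0.3, 0.5 or 0.7.

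**Variance.** Let s0 and s1 be the baseline and week-12 SDs.
- Change score: s0² + s1² − 2·rho·s0·s1
- ANCOVA: s1²(1 − rho²)
- Difference: (s0 − rho·s1)², which is never negative

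With s1 = s0, the ratio of ANCOVA to change variance is (1 − rho²)/[2(1 − rho)] = (1 + rho)/2.

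With s1 = 1.25·s0, the ratio is 1.5625(1 − rho²)/(2.5625 − 2.5·rho):
- rho 0.3: 1.4219/1.8125 = 0.78
- rho 0.5: 1.1719/1.3125 = 0.89
- rho 0.7: 0.7969/0.8125 = 0.98

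**Power.** The noncentrality is 10.7/(27·√ratio·√(2/36)) = 1.681/√ratio, with 70 df for change and 69 for ANCOVA (critical t 1.9944 and 1.9949). The change-score test has about 38% power throughout.

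| rho | Ratio, equal SDs | ANCOVA power | Ratio, s1 = 1.25·s0 | ANCOVA power |
|---|---|---|---|---|
| 0.3 | 0.65 | 54% | 0.78 | 47% |
| 0.5 | 0.75 | 48% | 0.89 | 42% |
| 0.7 | 0.85 | 44% | 0.98 | 39% |

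Simulation under equal SDs (20,000 trials at each rho, SD of change 27.1) agrees: 38% for change at every rho, and 53%, 47% and 43% for ANCOVA.

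In patient numbers, ANCOVA on 72 patients under equal SDs matches a change-score analysis of 72/0.65 = 111, 72/0.75 = 96 or 72/0.85 = 85.

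**Smaller effect.** The systematic review cited in the Background gives a mean difference of 5.76 points. With the same SD and equal variances, power is about 15% for change and 20%, 18% and 16% for ANCOVA.

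**The case against.** The planned test is valid. Randomisation makes the expected baseline difference zero, regression to the mean affects both arms alike in expectation, and the change score does use the baseline. This stands: the issue is precision, not bias.

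The gain is also not guaranteed. Entry requires a PTSD diagnosis, which may narrow the baseline spread, while week-12 scores may run from remission to non-response. If the week-12 SD is 1.5 times the baseline SD, the ratios are 0.87, 0.96 and 0.998 and ANCOVA power is 43%, 39% and 38%, close to the change score. This stands too, and it is why the equal-variance figures should be read as favourable. It does not reverse the comparison: ANCOVA cannot lose more than the cost of one degree of freedom.

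Using a different model at 24 weeks, after drug withdrawal, is not a contradiction, and an article may leave covariates to a fuller plan. But the article does name the 12-week model, and it names one without a covariate.

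A reader might go further and infer that the primary test is the group main effect, since treatment group is the only factor named. That effect averages baseline and week 12 and halves the treatment difference to 10.7/2 = 5.35; simulated power would be 22%, 16% and 11% at rho 0.3, 0.5 and 0.7. The documents do not support this reading. Naming a factor does not select its main effect as the test, and an endpoint defined as change compared between groups points to the group-by-time term. What remains is that the tested term is not named, which leaves room for misreading.

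Observed power drives no decision in the plan, so it adds little weight.

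**Conclusion.** The point holds as a matter of efficiency. The primary comparison is in effect a change-score test without a baseline covariate. It is valid, but generally less precise than the ANCOVA that the data already allow.

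For a 10.7-point effect, power rises from about 38% to between 44% and 54% if the two variances are equal, and to between 39% and 47% if the week-12 SD is 1.25 times the baseline SD. These figures rest on assumed correlations of 0.3 to 0.7 and on an SD of change back-calculated from one small trial. The direction does not rest on them: beyond one degree of freedom, ANCOVA does no worse at any correlation or SD ratio.

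The change is worth making. It does not show that the planned analysis is biased, or that it would test a diluted effect.

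**What to change.** State the primary analysis as ANCOVA of week-12 CAPS total, with treatment as the factor and baseline CAPS total as the covariate. Report the adjusted mean difference with its 95% confidence interval. The treatment term then is the test, which also removes any doubt about which ANOVA effect is meant.

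Use the same model for the other scales that have their own baseline score (BDI, GAF, CGI-S). Do not extend it to CGI-I, which is already rated relative to baseline.

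As a minor addition, drop observed power and let the confidence interval show what a non-significant result does and does not exclude.

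The cost is a change of wording and one error degree of freedom (70 to 69). No new data are needed, and the analysis is routine in standard statistical software.

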### Research Goals

The trial will compare the efficacy of topiramate with placebo in the treatment of PTSD, and will study its tolerability through the drop out rate in each group. The primary hypothesis is that topiramate will be superior to placebo in the treatment of PTSD. Secondary research goals includes studying the efficacy of topiramate in social adjustment, functioning and quality of life. Additionally, evaluating treatment adhesion, and studying the efficacy of topiramate in depressive symptoms.

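### The 5% rule for all comparisons should be reconciled with the Bonferroni rule for secondary outcomes (a minor wording conflict), and Holm's procedure could replace Bonferroni at little cost

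*Protocol article*

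**What the plan says.** All the relevant text is in the protocol article, mostly under Statistical Analysis.

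- The first paragraph describes the main model: "The data analysis will be conducted using a ANOVA comparing each scale during the 2 continuous measures from baseline and 12 weeks". The significance rule follows directly: "The confidence level that will be used for all comparisons will be 5% (p < .05". A significance level is clearly meant, although the word used is confidence.
- The second paragraph names one primary endpoint: "The primary efficacy endpoint will be the change in PTSD Scale- CAPS total score from baseline to the final visit at 12 weeks".
- It lists the secondary outcomes as "the Clinical Global Impressions (CGI), the Beck Depression Inventory (BDI), the Global Assessment of Function (GAF), and the PANAS scales", and adds: "Other secondary analyses will include an evaluation after 24-weeks".
- It then sets the multiplicity rule: "On all secondary outcomes, the Bonferroni correction will be applied for testing multiple variables".

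Neither paragraph refers to the other, and neither gives the number of tests or the corrected threshold. Sample Size repeats the overall level, "considering a 5% probability of type I error (significance level), and 20% for type II error (power test of 80", for a two-sided test with 36 patients per arm.

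**The concern.** The 5% sentence comes straight after a sentence about analysing every scale, so on its face it covers BDI, GAF and CGI as well as CAPS. The Bonferroni sentence also claims all secondary outcomes. A secondary p-value below .05 but above the Bonferroni cut would be significant under one sentence and not under the other. If the choice were left open until the data were seen, a claim about depression, functioning or global impression could turn on which sentence was followed.

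A separate matter is efficiency. Once a Bonferroni correction is accepted, Holm's step-down version gives the same protection under the same conditions and can only add rejections. In a trial of 72 patients that is worth considering.

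**Working it through.** **Inputs from the protocol article.** Overall level 0.05, two-sided; 36 per arm (Sample Size). Secondary outcomes CGI, BDI, GAF and PANAS, so m = 4, or m = 5 if the two CGI scales in Measures count separately (Statistical Analysis). The plan states no corrected threshold, so there is no figure of its own to reproduce.

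**Assumptions, not in the document.** A standardised effect d = 0.65 on each outcome with a real effect, correlation 0.5 between outcomes, and normal test statistics.

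**Step 1: the disputed band.** The Bonferroni cut is 0.05/m.
- m = 4: 0.05/4 = 0.0125, so p-values from .0125 to .05 are in dispute.
- m = 5: 0.05/5 = 0.010.

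**Step 2: family-wise error if the correction were ignored.** For independent tests this is 1 − 0.95^m.
- m = 4: 1 − 0.95^4 = 18.5%.
- m = 5: 1 − 0.95^5 = 22.6%.
- At correlation 0.5, simulation gives about 15.5% (m = 4) and 18.4% (m = 5).
- With Bonferroni and independent tests: 1 − (1 − 0.0125)^4 = 4.9%.

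**Step 3: Holm against Bonferroni, m = 4.** Bonferroni compares every p-value with .0125. Holm orders them from smallest to largest, compares them in turn with 0.05/4 = .0125, 0.05/3 = .0167, 0.05/2 = .025 and .05, and stops at the first failure. The first step is the same, so the chance of at least one rejection is identical. Later steps are more lenient, so Holm never rejects less.

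Bonferroni power for one real effect: the mean of the test statistic is 0.65 × √(36/2) = 2.758 and the two-sided critical value at .0125 is 2.498. Power is Φ(2.758 − 2.498) = Φ(0.260) = 60%.

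Simulated average power per real effect, correlation 0.5:

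| Real effects among the four | Bonferroni | Holm |
|---|---|---|
| 4 | 60% | 69% |
| 3 | 60% | 65% |
| 2 | 60% | 63% |
| 1 | 60% | 60% |

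At d = 0.5 the figures are 35% against 42% with four real effects, and 35% against 37% with two. At d = 0.65 with four real effects, the chance of at least one rejection is about 87% under both methods.

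**The case against.** The strongest reply is that there is hardly a conflict. A Bonferroni correction is always applied to some stated level, and 5% is that level. The specific instruction for secondary outcomes governs the general one, and corrected p-values compared with .05 satisfy both sentences. That stands. A reader might infer that the plan permits a family-wise error of 18.5% to 22.6%. The document does not support this: those figures arise only if the analyst disregards an explicit correction. The primary comparison is a single test and is not affected.

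A reader might also infer that choosing Bonferroni is an error. It is not. It is valid and prespecified, and preferring Holm is an improvement on offer rather than a correction. Nor should the gain be quoted only for the case where all four effects are real. It shrinks to about two percentage points with two real effects and vanishes with one. The document gives no effect sizes or correlations for these scales, so every power figure is conditional.

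Finally, a condensed article may leave thresholds to a fuller document. That is why the absence of a stated divisor is not the point here. What remains is that two sentences in the text as printed both claim all of the same tests and neither yields to the other.

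**Conclusion.** The point holds as a minor wording conflict together with an inexpensive improvement. The wording should be reconciled because, with four outcomes, the literal readings disagree for p-values from .0125 to .05; the sensible reading already settles this in favour of the correction. Holm would add about 9 percentage points of average power per real effect if all four outcomes respond, about 5 if three do, 2 to 3 if two do, and none if one does. Those gains assume four outcomes, 36 per arm, correlation 0.5 and d = 0.65. That Holm controls the same family-wise error and never rejects less does not depend on those assumptions, provided that the two methods are applied to the same family.

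**What to change.** In the first paragraph of Statistical Analysis, replace the 5% sentence with wording such as: *The two-sided significance level is 5% for the primary CAPS comparison; for the secondary outcomes, 5% is the family-wise level.*

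In the second paragraph, replace the Bonferroni rule for the listed outcomes with: *The 12-week secondary outcomes (CGI, BDI, GAF, PANAS) form one family tested with Holm's procedure at a two-sided family-wise level of 5%.* Say in the same place whether CGI enters as one measure or two, since that sets the family size.

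Leave the planned responder, completion and 24-week analyses as they are. The responder and completion comparisons serve the two stated aims (efficacy, with response defined there, and tolerability through dropout), so the edit should not reduce them to description or remove their level. If the sponsor meant the 24-week comparisons, or the social adjustment and quality-of-life goals ("Secondary research goals includes studying the efficacy of topiramate in social adjustment, functioning and quality of life"), to share the correction, list them in the family and apply Holm at that larger size.

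The cost is two sentences and no change to trial conduct. The downside is that Holm has no simple simultaneous confidence intervals to match its decisions. If such intervals matter to the sponsor, keeping Bonferroni and making only the first edit is acceptable.
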